### Compliance and losses to follow-up

Workshop attendance by control dyads is monitored and will be used to interpret study findings, as will attendance of the information session by experimental dyads. Social workers record the number of meetings held with dyads that later drop out. Dyads that withdraw their participation are reached by phone, once, and invited to return to the Research Center for a follow-up assessment. Posttests are conducted at home when most convenient for participants. Those refusing are asked whether they have committed their preferences in writing and, if so, to provide a copy of *My Preferences *completed. Concordance data are not available from dyads that refuse further involvement as such data cannot be collected over the phone.

### Potential limitations

People who agree to participate may differ to some extent from those who refuse. In particular, participants may be more favorable towards ADs - especially research ADs - than non-participants. Information gathered during the first telephone contact with prospective subjects will provide some data to compare participants with those who decline participation.

Participants are not explicitly informed of the study hypotheses. However, they cannot be blinded completely to group assignment. This design feature may exert some influence on their decision to complete *My Preferences*. However, it is unlikely to affect the primary outcome (prediction accuracy of substitute decisions) since dyad members are tested in separate rooms with vignettes that differ in part from those used at baseline. The use of control dyads partially controls for the Hawthorne effect on outcome measures. Furthermore, to ensure that participants who choose to express their preferences in writing understand the purposes and uses of written ADs, all participants are administered a brief knowledge questionnaire at the last posttest.

Every effort is made to keep research nurses blind to group assignment, including instructing participants not to reveal their group assignment. Unblinding may occur in some cases but this should not affect results since concordance is assessed by two nurses in separate rooms. While nurses may inadvertently discover that the dyad was exposed to the intervention (or not), this knowledge cannot impact concordance as they are unaware of the answers given by the other dyad member. Contamination is highly unlikely since controls do not meet their experimental counterparts and the consent form does not detail the tested intervention. Co-interventions are also unlikely given the relatively short duration of the intervention and scarcity of AD promotional efforts in the province of Quebec.

Last but not least, hypothetical vignettes do not generate the emotional reactions that characterize real-life situations. In addition, preferences may change as a result of declining health. Despite these drawbacks, the use of hypothetical scenarios in eliciting preferences for times of incapacity is common practice in advance care planning and research on substitute decision-making. More importantly, the intervention raises participants' awareness of the importance of updating ADs regularly.

### Statistical analyses

Persons who decline participation or drop out will be compared to trial participants with parametric or non-parametric two-sample tests (depending on the distribution of the data) and results used to judge the scope of study findings. The same tests will be used to compare participants' baseline characteristics across study groups. Potential confounders and compliance indices will be candidates for adjustment when testing the impact of the intervention on the outcome measures [82]. All analyses will be based on allocation to the intervention or control group (i.e. by intention-to-treat). To account for losses to follow-up, analyses will be conducted in duplicate, first restricting the sample to the dyads for which we have complete follow-up data, then using a conservative approach by which dyads that do not provide such data are assumed not to have documented preferences and their baseline concordance levels are used for imputation [83].

The primary analysis will involve calculating composite scores of agreement across health states for each dyad. Calculations will generate a total concordance score as well as sub-scores derived from restricting summations to the clinical or research vignettes. Growth-curve modeling implemented with SAS PROC MIXED will be used to compare composite scores across time points and groups, an approach that accounts for the within-dyad correlation over time and accommodates missing values [84,85]. To further elucidate the impact of the intervention, secondary analyses will involve applying the same statistical procedure to the concordance sub-scores. A multivariable logistic model will be used to compare group-specific completion rates of *My Preferences *6 months post-intervention. The financial impact of the intervention will be investigated with Student's *t *test for independent samples or its non-parametric equivalent.

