## Methods/Design

### Design and target population

The efficacy of the proposed intervention in improving prediction accuracy of substitute decision-making is assessed through a single-blind, stratified, randomized controlled trial with prediction accuracy measured at baseline, at the end of the intervention and 6 months later.

The study population is formed of dyads comprising a decisionally-competent older adult and the person he/she would choose to make healthcare decisions on his/her behalf in the event of incompetence (called "the proxy"). Eligible older adults are community-dwelling, French-speaking individuals aged 70 and over who live in the Eastern Townships of the province of Quebec and are likely free of cognitive deficits. Eligible proxies must live in the same region and be fluent in French.

Dyads are randomly assigned to the intervention or control group after stratification for two factors that may influence the success of the intervention: type of designated proxy (spouse *vs*. other) and self-report by the older adult of prior documentation of healthcare preferences (yes *vs*. no). Group allocation is made by reference to computer-generated blocked randomization lists prepared by a team member who has no involvement in delivering the interventions. Random block sizes from 2 to 8 were used within strata to reduce the predictability of group assignment and balance the number of dyads per arm.

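### Attendance after randomisation is admitted as an adjustment variable in the tests of the intervention effect, which conflicts in substance with the stated intention-to-treat analysis

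*Protocol article*

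**What the plan says.** The Statistical analyses section of the protocol article states: "Potential confounders and compliance indices will be candidates for adjustment when testing the impact of the intervention on the outcome measures". The outcome measures are not distinguished, so the primary outcome is included. The next sentence reads "All analyses will be based on allocation to the intervention or control group" and labels this intention-to-treat.

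The section Compliance and losses to follow-up shows what compliance means: "Workshop attendance by control dyads is monitored and will be used to interpret study findings, as will attendance of the information session by experimental dyads". For the home meetings it says only: "Social workers record the number of meetings held with dyads that later drop out".

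The primary model is described thus: "Growth-curve modeling implemented with SAS PROC MIXED will be used to compare composite scores across time points and groups". No covariates are named for it. The guide-completion rate is to be compared with a multivariable logistic model, again without named covariates. Under Design and target population the article gives the baseline factors used in allocation (proxy type and prior documentation): "Dyads are randomly assigned to the intervention or control group after stratification for two factors that may influence the success of the intervention".

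**The concern.** Attendance is observed only after allocation and can depend on it. Under Trial interventions, two of the three experimental meetings take place in a home, a choice the article expects to reduce attrition, while controls always meet in groups. Attendance is also plausibly part of how the intervention works, since the article's summary of earlier reviews names delivery over several sessions as a feature of success.

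Conditioning on such a variable does two things:

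- **Selection.** If motivated dyads attend more and also agree more, then at a given attendance level the arm with lower overall attendance contributes the more motivated dyads. The comparison is no longer between randomised groups.
- **Mediation.** If the intervention acts through sessions attended, adjustment removes part of the effect the trial wants to measure.

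The measure also means different things by arm: a session on advance directives in one, health workshops in the other. At stake is the primary test. If attendance is higher in the experimental arm, the bias runs against the intervention, and an effective programme could be reported as ineffective.

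**Working it through.** **1. The plan's own figure.** Inputs from the Sample size section: 86 dyads per group, standardised difference 0.43, two-sided α = 0.05, t statistic. The noncentral t distribution gives power 80.06% at 86 per group and 79.6% at 85, so the stated 86 and 80% reproduce. For the number randomised, 120 × 0.90 = 108 and 108 × 0.80 = 86.4, which agrees with the projected 120, 108 and 86. None of this depends on the adjustment question.

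**2. Bias from adjusting for attendance when the intervention does nothing.** The documents give no attendance rates or correlations, so all inputs in this step are assumptions. Let U be a standard normal motivation score with correlation r to the outcome (in SD units). A dyad attends if U exceeds an arm-specific threshold, giving attendance pE in the experimental arm and pC in controls. In the regression of outcome on arm and attendance:

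- attendance slope = r × [φ(zE) + φ(zC)] / [pE(1 − pE) + pC(1 − pC)], where z is the normal quantile of p and φ the normal density;
- arm coefficient = −slope × (pE − pC).

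The density φ(z) is 0.1755 at 90% attendance, 0.3178 at 75% and 0.3863 at 60%.

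| pE / pC | Slope | Bias, r = 0.2 | Bias, r = 0.3 | Bias, r = 0.4 |
|---|---|---|---|---|
| 90% / 90% | 1.95r | 0 | 0 | 0 |
| 90% / 75% | (0.1755 + 0.3178) / (0.09 + 0.1875) = 1.78r | -0.05 | -0.08 | -0.11 |
| 90% / 60% | (0.1755 + 0.3863) / (0.09 + 0.24) = 1.70r | -0.10 | -0.15 | -0.20 |

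The bias is also 0 when r = 0, and its sign reverses if controls attend more.

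**3. Effect on the test.** Simulation with 86 per arm and r = 0.3, under the same model:

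| pE / pC | Type I error | Power for a true 0.43 SD |
|---|---|---|
| 90% / 90% | about 5% | 80% |
| 90% / 75% | about 8% | about 62% |
| 90% / 60% | about 16% | about 41% |

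**4. A second attendance model.** Here 0 to 3 sessions are attended. The attendance parameter is 0.9 in the experimental arm and 0.9, 0.7 or 0.5 in controls, and the intervention effect is proportional to sessions attended.

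- No true effect, r = 0.3: bias 0, -0.12 and -0.21 for the three control values; type I error about 5%, 11% and 23%.
- No true effect, r = 0.5: bias 0, -0.20 and -0.36; type I error about 5%, 24% and 52%.
- True effect 0.43, r = 0, so mediation only: adjusted estimate 0.43, 0.40 and 0.38; power 80%, 69% and 54%.
- Without the attendance term, the estimate is about 0.00 or 0.43 as it should be, with type I error near 5% and power near 80%.

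**5. Stratification factors, for comparison.** Omitting them left the simulated estimate unbiased (0.00 and 0.43, with 88 per arm). Type I error was 4.8%, 4.4% and 3.0% when they explained 5%, 10% and 20% of outcome variance. Including them at 86 per arm, with 0.43 / √0.95 and 0.43 / √0.90 in the t-test power calculation, raises power from 80% to 82.0% and 84.0%.

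**The case against.** The strongest reply is that the plan only makes compliance a candidate. The named growth-curve model lists no compliance term, the compliance section speaks of using attendance for interpretation, and every dyad is analysed in its allocated arm. This is right as a limit on the claim. A reader might infer that the primary analysis will be adjusted for attendance or that dyads will be regrouped; the text supports neither. The conflict is over what the arm coefficient estimates. The reply does not remove the point, because the sentence expressly covers the tests of the intervention effect, and the article states no rule for when a candidate enters.

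Three stronger readings are also tempting and do not hold:

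- **That leaving the stratification factors unfixed breaks the randomised comparison.** It does not. The estimate stays unbiased and the test slightly conservative. The covariate list may stand in the analysis plan, which is not shown.
- **That covariates will be chosen by baseline significance tests.** This rests only on the order of the sentences. The baseline interview also collects factors thought to influence the outcomes, and these could be the intended candidates.
- **That the bias will be about -0.15 SD.** That figure needs 90% against 60% attendance. A gap that wide is most easily imagined between home visits and workshops, but the experimental-arm attendance the article says it will use is that of the group information session. Home meetings are mentioned only as a count for dyads that later drop out.

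**Conclusion.** Wrong as written. The plan admits a post-randomisation variable, measured on different sessions in each arm, into the tests of the intervention effect, and in the next sentence claims an intention-to-treat analysis. If the option is used, the arm coefficient is not the effect of allocation.

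The size cannot be fixed from the documents. With no true effect the bias is 0 if attendance is equal across arms or unrelated to outcome. It is about -0.05 to -0.2 SD for correlations of 0.2 to 0.4 with attendance of 90% against 75% or 60%; the upper end is nearly half the 0.43 SD design effect (0.20 / 0.43 = 0.47). Larger values, such as -0.36, need a correlation of 0.5 and a wide attendance gap. The negative sign assumes higher attendance in the experimental arm. The finding itself does not depend on these figures. The sample size and stated power are unaffected.

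**What to change.** - In Statistical analyses, delete compliance indices from the candidates for adjustment.
- Limit adjustment in the effect models to baseline variables named in advance, preferably including proxy type and prior documentation, for a small gain in power.
- In the growth-curve model, keep baseline concordance as a response, with the intervention effect carried by the arm-by-time terms. Do not add it as a covariate as well. The logistic model for guide completion needs only arm and the named baseline variables.
- Use attendance descriptively, as the compliance section already foresees, or in a separately labelled complier-average analysis.

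The cost is a change of wording before analysis. The two stratification factors are already recorded for allocation, and 240 randomised dyads with 86 per group at completion still stand.

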### Trial interventions

#### Intervention in the experimental group

The proposed intervention was designed from literature reviews [6,39,40] and recent experimentations [31,33]. It integrates multiple methods to increase learning [46] and uses teaching tools adapted to normal aging changes [47]. The intervention consists of 2-hour meetings, once monthly, over three months. The duration of the intervention follows from the need for an incremental process that enables older adults to articulate preferences at their own pace and gradually integrate information on the benefits and limitations of ADs [28]. Furthermore, we expect repeated encounters to foster trusting relationships between dyad members and research personnel that are conducive to discussions on issues as sensitive as end-of-life care. The first and third meetings take place in the home of the older adult or proxy, a strategy likely to counter attrition [31]. The second meeting is an information session on ADs for groups of dyads.

Home meetings are led by trained social workers with extensive experience working with elders. The first visit begins with two thought-provoking vignettes that highlight the importance of communicating one's wishes about future medical care and research participation. The use of vignettes illustrating real-life experience has been shown to increase learning in elderly populations [47]. After eliciting reactions to the vignettes and exploring related issues, the facilitator summarizes the dyad-specific results of the concordance assessment and invites dyad members to discuss the reasons underlying their choices. Discussions seek to help older adults describe what makes their life worth living in specific, functional terms [48] and articulate their wishes, personal values and beliefs, so as to guide proxies in making decisions for them. Throughout the intervention, the social worker catalyzes discussion so that a shared understanding gradually develops between the older adult and his/her proxy.

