#### Intervention in the control group

Approximately once monthly over three months, dyads assigned to the control group are invited to attend a 2-hour health education workshop on healthy lifestyle and preventive practices. The three workshops are adapted from a health education program aimed at improving self-care skills that has been effective with elderly people [66]. The number of meetings between dyads and the research team is identical across groups. However, experimental dyads meet individually and in subgroups whereas controls always convene in subgroups. Health education workshops are given by experienced nurses and allow for interaction within and between dyads. Once the study is complete, the AD information session given to experimental dyads will be offered to controls.

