### Sample size

We are aiming for 86 dyads per group at study completion, which would provide 80% power to detect a standardized difference of 0.43 in overall prediction accuracy between the study groups (calculation based on the *t *statistic, two-sided α = 0.05, nQuery Advisor 6.0). The expected standardized difference was derived from Schwartz *et al*. [31] whose study resembles our own in many respects. The tested interventions are of comparable intensity and duration. Both include an AD educational component and devote a central role to proxies. Moreover, in both cases, prediction accuracy is measured with a composite index derived from combining proxy's ability to predict the older adult's preferences under various hypothetical scenarios.

Accounting for a drop-out rate of 10% at posttest 1 and 20% at posttest 2, 240 dyads will be randomized. As indicated in Figure 1, we started the recruitment process with a random list of 1,000 individuals who fulfill our first four inclusion criteria. This number should allow us to reach the target sample size, further accounting for sampled individuals who will be found ineligible (e.g., institutionalized or deceased, no longer reside in the study area, no proxy meeting study criteria), refuse to be interviewed, or decline study participation.

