**Figure 1 F1:**
[figure not shown]
**Study subjects flow chart (with estimated sample sizes in parentheses)**.

The above calculations assume that we will compare groups on posttest mean concordance scores as this allowed us to use the best available estimate of the likely effect of the intervention. However, our design involves repeated measurements of concordance over time that will be analyzed by growth-curve modeling, a more sophisticated approach that effectively uses all the available time points to estimate individual trajectories. Determination of suitable sample sizes for multilevel analyses is complex, in part because explicit formulas have not yet been derived for general models. However, simulations by Mass & Hox [86] show that between 50 and 100 units per group are needed to justify claims as to the absence of bias in standard error estimates. As shown in Figure 1, projected sample sizes are 120 units per group at baseline, 108 at posttest 1 and 86 at study completion. Since all data will contribute to some extent in estimating the model parameters, our approach to sample size estimation is conservative and protects against an underpowered study.

Lastly, as shown in Table 1, 86 dyads per group also provide sufficient power to detect a meaningful difference between groups for the secondary outcome.

**Table 1 T1:** Power to detect the intervention effect on documented preferences, according to three sources of information (*n *= 86 dyads per group, two-sided α = 0.05)

Source	Odds ratio (95% CI)	Event rate in the Control group	Event rate in the Experimental group	Power
Bravo *et al*. [39]	4.0 (1.6 - 10.4)	0.12*		95%
Patel *et al*. [87]	3.7 (1.5 - 9.4)	0.12*		92%
Pearlman *et al*. [10]		0.23	0.48	93%

* Derived from 13 RCTs included in our systematic review (mean = 0.12, sd = 0.182, range: 0 to 0.56) and applied to Patel *et al*. who did not report the mean event rate across control groups.

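### Dyads share facilitators and session groups within each arm, but the stated analyses allow only for correlation within a dyad; if outcomes correlate by group or facilitator, type I error exceeds 5%

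*Protocol article*

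**What the plan says.** The protocol article randomises single dyads (Design and target population) but delivers both programmes partly or wholly through shared people and shared sessions.

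- **Experimental arm.** Two of the three meetings are at home: "Home meetings are led by trained social workers with extensive experience working with elders". The other is an information session for several dyads together, in a small-group layout meant to promote interaction. The document does not say who leads that session.
- **Control arm.** All three workshops are in groups: "Health education workshops are given by experienced nurses and allow for interaction within and between dyads". The article itself notes the contrast: "experimental dyads meet individually and in subgroups whereas controls always convene in subgroups".
- **Analysis.** The only correlation named for the primary mixed model is in the clause "an approach that accounts for the within-dyad correlation over time and accommodates missing values". Guide completion is compared with a multivariable logistic model, and cost with Student's t test for independent samples or a non-parametric equivalent. No group or facilitator term is mentioned for any of them.
- **Sample size.** "We are aiming for 86 dyads per group at study completion, which would provide 80% power to detect a standardized difference of 0.43", from a t statistic with no design effect. The text under Figure 1 adds that all time points will contribute to the model and therefore calls the approach conservative.

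**The concern.** Session groups and named facilitators are formed after randomisation and differ by arm. Dyads guided by the same social worker, or who sit through the same session, may end up with more similar concordance scores, or a more similar readiness to complete the guide, than dyads who do not. The design depends on the mechanisms that could cause this: trust built with research staff, a social worker who drives the discussion, and group activities in which participants begin filling in the guide.

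A random effect for the dyad does not absorb variation between groups or facilitators, because that variation is shared across dyads. If it exists and is left out, the standard error of the arm comparison is too small. Part of an apparent programme effect could then come from one strong facilitator or a few lively groups, and the planned power would be overstated for a test that allows for this.

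**Working it through.** **Inputs from the document (Sample size).** Two-sided α = 0.05; standardised difference 0.43; 86 completers per arm; 80% power; 240 randomised ("Accounting for a drop-out rate of 10% at posttest 1 and 20% at posttest 2, 240 dyads will be randomized").

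**Inputs assumed.** Group size m and ICC are not given. The main case uses m = 8 with ICC from 0 to 0.05; the wider range uses m from 4 to 12.

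**1. The plan's own figure.** The noncentral t calculation with d = 0.43 gives power of 79.6% at 85 per arm and 80.1% at 86, so 86 is reproduced. Sequential attrition gives 120 × 0.9 × 0.8 = 86.4, which matches "projected sample sizes are 120 units per group at baseline, 108 at posttest 1 and 86 at study completion". The arithmetic is correct for independent dyads, with almost no slack.

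**2. Formulas.**
- Design effect when both arms are clustered: DE = 1 + (m − 1) × ICC.
- Variance ratio when one arm is clustered: V = (1 + DE)/2. With both arms clustered, V = DE.
- Type I error of a test that ignores the clustering: 2 × [1 − Φ(1.96/√V)].
- Power of a test that allows for it: Φ(0.43/√(2V/86) − 1.96). This normal approximation gives 80.5% at V = 1, against 80.1% by the t distribution.

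**3. Results for m = 8, 86 per arm.**

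| ICC | Clustered | V | Type I error, unadjusted test | Power, adjusted test |
|---|---|---|---|---|
| 0 | – | 1.00 | 5.0% | 80% |
| 0.01 | one arm | 1.035 | 5.4% | 79% |
| 0.01 | both arms | 1.07 | 5.8% | 78% |
| 0.02 | one arm | 1.07 | 5.8% | 78% |
| 0.02 | both arms | 1.14 | 6.6% | 75% |
| 0.05 | one arm | 1.175 | 7.1% | 74% |
| 0.05 | both arms | 1.35 | 9.2% | 68% |

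Example, one arm at ICC 0.05: DE = 1 + 7 × 0.05 = 1.35; V = 2.35/2 = 1.175; 1.96/√1.175 = 1.81; type I error = 7.1%.

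A simulation of the both-arms case (20,000 runs, t test, m = 8) gave 5.9%, 6.4% and 8.9% at ICC 0.01, 0.02 and 0.05, in line with the formula. For m from 4 to 12 and ICC from 0.01 to 0.05, with both arms clustered, type I error runs from 5.4% to 11.5%.

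**4. Does using baseline remove the problem?** Assume a baseline–posttest correlation of 0.5 (not in the document) and clustering that arises only after baseline. The residual variance factor becomes 1 − 0.5² = 0.75, and the clustering part stays at V − 1.
- Power with both arms clustered is Φ(0.43/√(2 × 0.89/86) − 1.96) = 85% at ICC 0.02. At ICC 0.05, with 1.10 in place of 0.89, it is 77%.
- The variance ratio relevant to type I error is 0.89/0.75 = 1.19 and 1.10/0.75 = 1.47, so the unadjusted test runs at about 7.2% and 10.6%.

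Baseline information can restore power, but it does not repair the error rate.

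**The case against.** **The clause on within-dyad correlation describes a property of the method and need not list every random effect.** This is fair for the mixed and logistic models: an unseen analysis plan could add a term. Only the cost t test is fixed closely enough to exclude one. But the article does fix the sample size without a design effect and does call that conservative, so the point goes beyond missing detail.

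**Equal clustering in both arms is doubtful.** This stands. Control workshops concern healthy lifestyle, and it is hard to see how they would correlate proxies' accuracy about treatment preferences. Two of the three experimental meetings are specific to the dyad. The one-arm rows are therefore the more plausible ones.

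**If neither programme affects any dyad, individual randomisation protects the 5% level.** This is correct. Inflation arises where group or facilitator effects are real but average to zero, and where the inference is meant to reach beyond these particular facilitators. The Discussion, which envisages extending the intervention more widely, suggests that broader target.

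**The repeated-measures analysis may have more power than 80%.** It may, as step 4 shows, but that does not answer the type I error point. Guide completion also has slack: with DE 1.35 in both arms, the Table 1 powers would still be about 83% to 88%.

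A reader might infer that type I error does exceed 5%, that only a few facilitators are used, or that 86 per group is a miscalculation. The document supports none of these. It gives no ICC, no facilitator count and no group size, and the 86 is right on its stated basis.

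**Conclusion.** The point holds in conditional form. Group and facilitator delivery is documented in both arms, and the stated analyses make no allowance for it. If outcomes correlate within session group or facilitator, standard errors are understated and type I error is above 5%.

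The size rests on an assumed group size and ICC. In the more plausible one-arm case the excess is modest over the ICC range examined, and it is larger if both arms cluster. Clustering by facilitator could matter more, because each would see more dyads than sit in one session, but without a facilitator count no figure for it can be tied to the document.

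The 80% power is correct for independent dyads in a posttest-only t test. Calling the sample size conservative is justified only against the unused time points, not against clustering.

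**What to change.** 1. Record the session group and the facilitator for every dyad. Attendance is already monitored and social workers already log meetings for dyads that drop out (Compliance and losses to follow-up), so the burden is small. Enrollment has begun, and without these identifiers the analysis cannot be corrected later.
2. Add to the PROC MIXED model a partially nested random effect for session group, acting after baseline and at least in the experimental arm, with a small-sample degrees-of-freedom correction.
3. Use cluster-robust errors or an equivalent term for the logistic and cost comparisons.
4. If there are few social workers, show results by social worker descriptively, since a variance for so few units would be poorly estimated.
5. State that the 80% power assumes no clustering by group or facilitator, and qualify the claim of conservatism, ideally with power over a range of ICCs.

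The cost is a more careful model specification and, if the ICC is above zero, somewhat wider confidence intervals and a somewhat lower stated power. If the ICC is near zero, the results should change little.
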